## Subjects

All patients who have been enrolled into the PEP programme will be included in the evaluation on process of care for each audit cycle; whereas all enrolled subjects who have been recruited for more than 12 months in the programme will be included in the evaluation on the clinical outcomes of care for each audit cycle.

To determine a difference of programme performance and impact between group (PEP participants and non-participants). A cohort of all eligible DM patients under care of HA GOPC at 1 Sep 2009 would be included for the monitoring of the changes in clinical and service utilization outcomes from Sep 2009 to Sept 2015.

550 patients who have enrolled into the PEP and 550 who have not taken part in the PEP will be invited in person from the general outpatient clinics by trained research assistants at the beginning of each evaluation cycle to take part in a telephone survey on patient reported outcomes for each cluster and written consent will be obtained (appendix A). All subjects who have given consent to the telephone follow-up survey will be interviewed by telephone within four weeks, at 6, 12, 36 and 60 months from recruitment to answer the SF-12 Health Survey on quality of life (QOL), the patient enablement Instrument, the Global Rating Scale (GRS) change in health, and a structured questionnaire on private service utilization rates.

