## Data Collection

Evaluation on structure and process

The co-ordinator of each participating clinic and all participating NGO will be asked to complete the structure of care questionnaire (appendix B). Anonymized data will be retrieved from the computerized medical record system (CMS) by the HA Statistics team to determine the patient recruitment rate, enrollment rate, attendance rate, compliance with assessment as per protocol, number of investigations and referral rate.

Evaluation on outcomes of care

Anonymized data on HbA1c, blood pressure (BP), low-density lipoprotein (LDL), body mass index (BMI) and annual attendance rates for GOPC, specialist outpatient clinic (SOPC) , accident and emergency (A&E) and hospital attendance rates, patient knowledge on disease at baseline and 12 months will be retrieved from the CMS by the HA Statistics team. The audit cycle will be repeated annually over a period of 5 years. This data will be extracted are shown in the data collection form in appendix C.

The 550 patients in the PEP programme who are willing to take part in the telephone survey will be contacted by a trained research assistant who will obtain verbal consent from each patient. Each patient will then answer the Chinese (Hong Kong) Short Form-12 version 2 (SF-12v2) Health Survey within one month from enrolment, and then at 6, 12, 36 and 60 months to repeat the SF-12v2 together with the Patient Enablement Instrument (PEI), Global Rating Scale (GRS) of change in health condition and private service utilization (appendix D).

- 1. The Chinese (Hong Kong) Short Form-12 version 2 (SF-12v2) Health Survey is a generic measure HR QOL. It has been validated and normed on the general Chinese population in Hong Kong (Lam, Wong et al. 2010). It measures eight domains on physical functioning, role physical, bodily pain, general health, vitality, social functioning, role emotional and mental health on a scale range from 0 to 100. A higher score indicates better HRQOL. The eight domain scores can be summarized into two summary scores, the physical (PCS) and mental (MCS) component summary.

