## Outcome measures

**Primary**

- The proportion of clinics/NGO that have satisfied each of the set structure criteria.
- The proportion of patients who have complied with the criterion process of care.
- The proportion of DM patients who have achieved a HbA1c level <7%.
- The proportion of HT/ DM patients who have achieved the target blood pressure.
- The estimated 10-year cardiovascular disease risk.

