## Data analysis

1. Descriptive statistics on standard of care will be calculated, including percentage of centers meeting each structure criterion, percentage of subjects enrolled, dropped out, completion of the programme, receiving criterion process, investigations and referral per protocol, and percentage of subjects achieving the criterion outcome.
2. The change in clinical, service, and patient reported outcomes after the PEP programme at baseline, 6, 12, 36 and 60 months will be compared by paired sample t-test. The audit cycle will be repeated annually over a period of 5 years.
3. Independent sample t-test or Chi square test as appropriate will be used to compare the clinical and service utilization outcomes between PEP patients and controls.
4. Independent sample t-test or Chi square test as appropriate will be used to compare the clinical and service utilization outcomes between results in achieved in different audit cycles.
5. Cost effectiveness analysis (CEA) by mathematical modeling will be carried out by using cost and clinical outcome data provided by the HA, as well as quality-of-life and private service utilization cost data collected by the telephone surveys.

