**Patients require special treatment:**

| **Data Required** | **Number of  patients** | **Time (in days) from problem recognition** |
| --- | --- | --- |
|
| Identified to have problem being given treatments per protocol |  |  |
| Referred for additional service |  |  |
| Refused additional service |  |  |

| **Time (Month)** | **Data required** |
| --- | --- |
| 0, 12, 24, 36 and 48 | **Clinical data** |
| HbA1c |
| Systolic BP |
| Diastolic BP |
| BMI |
| LDL-C |
| **Service utilization** (in the past 12 months) |
| Number of hospitalization |
| Number of A&E attendance |
| Number of GOPC consultation |
| Number of SOPC consultation |
| 0 and 6 months | **Patient reported** |
| Disease knowledge score |
| QoL score |
| PEI* |
| GRS* |

BP = Blood Pressure; BMI = Body Mass Index; LDL-C = Low density Lipoprotein Cholesterol; GOPC = General Outpatient Clinic; SOPC = Specialist Outpatient Clinic; KAP = Knowledge, Attitude and Practice.

*Measured at 6 months only.

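### Data analysis item 4 compares audit cycles with independent-sample tests although the same patients recur in successive cycles, so its standard errors are too large and the test is conservative

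*Protocol*

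**What the plan says.** Item 4 of the Data analysis section applies an independent-sample t-test or a chi-square test, as appropriate, to "compare the clinical and service utilization outcomes between results in achieved in different audit cycles".

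The Subjects section defines who enters the clinical-outcome evaluation of each cycle: "all enrolled subjects who have been recruited for more than 12 months in the programme will be included in the evaluation". There is a lower limit on time since recruitment and no upper limit. The Data Collection section adds: "The audit cycle will be repeated annually over a period of 5 years". The Appendix C extraction form schedules clinical and service-utilization data at months "0, 12, 24, 36 and 48".

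Two other provisions might seem to cover the problem.
- Item 2 specifies a paired t-test, but for change over follow-up, not for one cycle against another.
- The Subjects section describes new samples of 550 plus 550 at the start of each cycle, but only for the telephone survey of patient-reported outcomes, which item 4 does not analyse.

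No section limits a cycle to newly eligible patients or adjusts the cycle comparison for time since enrolment.

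**The concern.** Membership of a cycle is cumulative. A patient evaluated in cycle 1 still meets the 12-month rule in every later cycle, so two successive cycles share patients. The tests named in item 4 require two independent groups and leave out the covariance that the shared patients create. When a patient's values are positively correlated from year to year, as is usual for HbA1c, blood pressure and attendance, the standard error of the difference is overstated and real differences between cycles are harder to detect.

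There is a second, conditional issue. If patients carried over contribute their current yearly value, later cycles hold patients further from enrolment, and a difference between cycles mixes a change in programme delivery with time since enrolment. The Feedback section returns the results of each evaluation to the programme team to guide quality enhancement, so a misread cycle comparison could affect those decisions.

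The test is named in the protocol itself, so this is not a detail left open for a later analysis plan.

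**Working it through.** **The plan's own figure.** The protocol gives no sample size, power or variance for a comparison between cycles. Its only calculation concerns quality of life in the telephone survey. That one reproduces: an effect of 0.3, 80% power and two-sided 5% give 175 per group, 350 in total. For dropout, 175 / 0.75^4 = 553, against 550 stated. It does not bear on item 4.

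**Inputs.** From the protocol: independent-sample tests (Data analysis, item 4), cumulative membership (Subjects), annual cycles over 5 years (Data Collection). Assumed here, because the protocol does not give them: equal yearly intake N, no loss, equal variance s² in each cycle, and within-patient correlation rho of 0.4 to 0.7.

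**Formula.** With n1 and n2 patients in two cycles and m shared, the true variance of the difference in means is

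s²(1/n1 + 1/n2 − 2·m·rho/(n1·n2)).

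The independent test uses s²(1/n1 + 1/n2). The same holds for proportions, with rho the correlation of target attainment.

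**Cycle 1 against cycle 2.** Here n1 = N, n2 = 2N, m = N.
- True variance: s²(1.5 − rho)/N. Assumed variance: 1.5·s²/N. Ratio: 1 − 2·rho/3.
- rho = 0.4: ratio 0.733, standard error too large by 1/√0.733 = 1.17.
- rho = 0.7: ratio 0.533, standard error too large by 1/√0.533 = 1.37.
- Actual level = 2·(1 − Φ(1.96/√ratio)) = 0.022 at rho 0.4 and 0.007 at rho 0.7.

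A simulation of this comparison at rho 0.3, 0.5 and 0.7 gave 0.028, 0.017 and 0.007, against 0.028, 0.016 and 0.007 from the formula.

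**Later cycles.** Under equal intake, cycle k holds k intakes, and the share carried over from the previous cycle is (k − 1)/k: 50%, 67%, 75% and 80% for cycles 2 to 5. The variance ratio for cycle k against k + 1 is 1 − 2k·rho/(2k + 1). For cycle 4 against 5 it is 0.644 at rho 0.4 and 0.378 at rho 0.7, so the standard error is too large by 1.25 to 1.63.

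**Which value does a carried-over patient contribute?** The protocol supports two readings.
- *Current yearly value.* Hypotheses 2 and 3 and Appendix C refer to months 12 to 48. Under equal intake and no loss, mean time since enrolment is then (k + 1)/2 years: 1.0, 1.5, 2.0, 2.5 and 3.0 over cycles 1 to 5. An assumed within-patient drift of 0.05 to 0.10 SD per year would produce a difference of 2 × 0.05 = 0.10 to 2 × 0.10 = 0.20 SD between cycles 1 and 5 with no change in programme quality.
- *12-month value only.* The Data Collection section speaks of retrieval at baseline and 12 months, repeated annually. Time since enrolment is then fixed and the mixing disappears. But carried-over patients supply the identical value to both cycles, so rho = 1 for them, the variance ratio is 1/(2k + 1), and the standard error is too large by √(2k + 1), that is 1.7 (k = 1) to 3.0 (k = 4).

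Independence fails under both readings.

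**The case against.** The strongest reply is that little of consequence depends on item 4, and much of this stands. None of the six hypotheses is a contrast between cycles. The Methods and Feedback sections frame the audit mainly as a comparison with set standards. The descriptive results of item 1 and the comparison with controls in item 3 are untouched.

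The following stronger inferences are tempting, and the protocol does not support them.
- *False claims of improvement from the dependence.* The direction is the opposite: with positive correlation the actual level falls below 5%.
- *A definite loss of power.* A figure would need a contrast sized at some known power, and the protocol sizes none. Clinical data come from all eligible enrolled patients, and that number is not stated. In a very large cohort the loss may matter little.
- *Certain confounding of cycle with duration.* It arises only on the yearly-value reading. What grows there is time since enrolment, not necessarily exposure, because patients can complete the programme.
- *The same fault in process measures.* The Subjects section does include all enrolled patients in the process evaluation of each cycle, but item 4 covers only clinical and service-utilization outcomes.

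None of this removes the core point: a named test assumes independence that the protocol's own inclusion rule breaks.

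**Conclusion.** The point holds in a limited form. Item 4 is wrong as written, because cumulative cycles cannot be compared as independent samples. With half of cycle 2 carried over and rho of 0.4 to 0.7, the standard error is 17% to 37% too large and the actual level of a nominal 5% test is 0.022 to 0.007. The overlap, the absence of loss and rho are assumptions; the direction needs only some overlap and positive correlation. The effect on power cannot be stated without the cohort size. Mixing with time since enrolment is conditional on which value carried-over patients contribute, and the protocol should settle that.

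This should be corrected before cycles are compared. It is not critical, since the error is conservative and item 4 is a supporting comparison.

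**What to change.** Amend item 4 in one of two ways, and state which value each patient contributes to a cycle.

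1. Compare 12-month outcomes between non-overlapping intakes, so that each cycle contains only patients newly reaching 12 months. The t-test and chi-square test then have independent samples, and time since enrolment is held fixed. The cost is fewer patients per cycle: under equal intake, cycle 5 would use one intake in five.
2. Keep the cumulative cycles and use GEE or a mixed model clustered on patient, logistic for target attainment, with cycle and time since enrolment as terms. Because calendar cycle is intake plus time since enrolment, the three are linearly dependent. The plan must state that the model separates cycle from duration only if there is no intake effect.

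The first is the simpler repair. Both use data already extracted and need only revised wording and a pseudonymous patient key that links the annual extracts.

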***Feedback***

The full analysis on the standards of care will be carried out at 15, 30 and 45 months from the start of the programme to evaluate whether the set standards of care on structure, process and outcome have been achieved. The results of each evaluation on the performance of the programme will be fed back to the programme team to identify changes in quality criteria and standards and quality enhancement strategies to be implemented.

Timeline of Study

| **Dates** | **Tasks** |
| --- | --- |
| Apr 2010 – Jun 2010 | - Recruitment of research assistants - Literature review - Development of the preliminary QOC evaluation framework |
| Jul 2010 – Sep 2010 | - Refine the QOC evaluation framework - IRB application - Training of interviewers |
| Oct 2010 – Jan 2011 | - Collection of data on structure from each participating clinic and NGO - Retrieval of data on process of care, and clinical and service outcomes from HA records - Collection of data on PRO (by telephone interview) |
| Apr 2011 – Jun -2011 | - Collection of data on PRO (by follow-up telephone interview) - Interim analysis of QOC data - Feedback of interim analysis results to PEP programme team - Implementation of quality enhancement strategies if needed |
| Sep 2011 – Oct 2014 | - Retrieval of data on process of care, and clinical and service outcomes from HA records - Four cylces of data analysis on QOC of the programme - Feedback on results on QOC to PEP programme team - Implementation of quality enhancement strategies if needed |
| Nov 2014 – Apr 2015 | - Prepare final report for submission to the HA - Preparation of manuscripts for publication |

QOC = Quality of Care; PRO = Patient reported outcomes.

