## Hypotheses

The following hypotheses will be tested:

1. The criteria on structure and process should be achieved by all participating clinics and NGO;
2. More patients with DM will achieve the target HbA1c after 12, 24, 36 and 48 months in the PEP programme;
3. More patients with HT or DM will achieve the target blood pressure levels after 12, 24, 36 and 48 months in the PEP programme;
4. In longer terms, HT/ DM patients will have reduced cardiovascular risks and fewer complications;
5. Patients should report an improvement in quality of life (QOL), enablement and overall health condition after the PEP programme;
6. Patients who take part in PEP programme should not have any increase in service utilization rates.

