## Sample size calculation

The sample size for the evaluation on QOL change is estimated to detect a minimally clinically important difference (MCID) in health-related quality of life (HRQOL) studies, which is equivalent to Cohen’s small effect size of 0.3 (Cohen 1988). A sample size of 350 patients in total (175 PEP participants and 175 non-participants) is needed in order to have 80% power and 95% confidence interval estimated by independent t-test to detect a small effect size (Erdfelder, Faul et al. 1996). Therefore, 1100 patients (550 PEP participants and 550 non-participants) will need to be recruited to account for 25% dropouts each follow-up (4 times).

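### The study calendar ends before the 60-month patient-reported outcomes behind the sample size can be collected, and the paired-test visits do not match the clinical extraction schedule

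*Protocol*

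**What the plan says.** Four parts of the protocol set time points.

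- **Survey outcomes.** Under Subjects, consenting patients are "interviewed by telephone within four weeks, at 6, 12, 36 and 60 months from recruitment". The Abstract, Data Collection and the secondary outcomes carry the same horizon to month 60.
- **Clinical outcomes.** Hypothesis 2 reads "More patients with DM will achieve the target HbA1c after 12, 24, 36 and 48 months in the PEP programme"; hypothesis 3 uses the same four time points for blood pressure. Appendix C extracts clinical and service data at months "0, 12, 24, 36 and 48", and lists the patient-reported items at 0 and 6 months only.
- **Analysis.** Data analysis, item 2, takes clinical, service and patient-reported changes together; these "at baseline, 6, 12, 36 and 60 months will be compared by paired sample t-test".
- **Calendar.** Under Feedback: "The full analysis on the standards of care will be carried out at 15, 30 and 45 months from the start of the programme". The timeline in the same section places PRO interviews in Oct 2010 to Jan 2011 and Apr to Jun 2011. It places record retrieval and four analysis cycles in Sep 2011 to Oct 2014. The last row, Nov 2014 to Apr 2015, is to "Prepare final report for submission to the HA" and to write manuscripts. Under Subjects, however, the diabetes cohort is followed to Sept 2015.

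On numbers, Sample size calculation states: "Therefore, 1100 patients (550 PEP participants and 550 non-participants) will need to be recruited". The reason given is 25% loss at each of four follow-ups.

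**The concern.** Both the visit schedule and the calendar are fixed in the protocol, and they conflict, so this is not detail left to an analysis plan. The last survey visit is a named secondary outcome and drives the size of the survey, yet it lies beyond the last scheduled data collection, the last analysis and the final report. For the record-based outcomes, item 2 names two visits at which Appendix C extracts nothing and omits two at which it does.

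A team following the protocol would have to decide for itself which time points were meant. A reader of the report could not tell a visit that was never feasible from one that was dropped after the data were seen. Survey patients would also have been recruited in numbers justified by a visit that the report cannot contain.

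**Working it through.** **1. The plan's own sample size.** Inputs from Sample size calculation: effect size 0.3, 80% power, independent t-test, 25% loss at each of four follow-ups. Two-sided alpha of 0.05 is assumed from the stated 95% confidence.

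- Evaluable per group: n = 2(1.96 + 0.84)²/0.3², which rounds up to 175. The t-test version gives 175.4. The stated 175 reproduces.
- Recruited per group: 175/0.75⁴ = 553.1, against 550 stated. This reproduces within rounding, so the 550 depends on the fourth follow-up, which is month 60.

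**2. When month 60 falls.** Inputs from the timeline.

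| Event | Date |
|---|---|
| First survey interviews | Oct 2010 to Jan 2011 |
| Last PRO collection scheduled | Apr to Jun 2011 |
| Retrieval and analysis end | Oct 2014 |
| Report and manuscripts end | Apr 2015 |
| Cohort follow-up ends (Subjects) | Sept 2015 |
| Month 60, first intake | Oct 2015 to Jan 2016 |

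Month 60 is 12 to 15 months after Oct 2014 and 6 to 9 months after Apr 2015. Counting from recruitment, up to four weeks before the interview, moves this by at most about a month. Survey patients are invited at the start of each cycle, so later intakes fall later still. Working backwards, month 60 by Apr 2015 needs enrolment by Apr 2010, before the ethics application (Jul to Sep 2010). The 12- and 36-month calls have no slot in the calendar either.

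**3. What losing month 60 does to the numbers.** The same rule with three follow-ups gives 175/0.75³ = 414.8, so 415 per group or 830 in total. If 550 are recruited:

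- at 36 months, 550 × 0.75³ = 232 remain per group, with power about 90%;
- at 60 months, 550 × 0.75⁴ = 174 remain per group, with power about 80%.

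**4. Item 2 against Appendix C, clinical and service outcomes.**

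| Month | Paired test (item 2) | Extracted (Appendix C) | Hypotheses 2 and 3 |
|---|---|---|---|
| 6 | yes | no | no |
| 12 | yes | yes | yes |
| 24 | no | yes | yes |
| 36 | yes | yes | yes |
| 48 | no | yes | yes |
| 60 | yes | no | no |

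Only 12 and 36 agree in all three.

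**5. Month 48.** The last listed full analysis is at month 45. Since 45 is less than 48, no participant can have 48 months in the programme at that analysis, whatever the start date. The timeline separately runs four cycles to Oct 2014, and 48 months by then requires enrolment by Oct 2010. The programme start is not given. Under assumed starts of Sep 2009, Apr 2010 or Oct 2010, month 45 is Jun 2013, Jan 2014 or Jul 2014, and Oct 2014 is month 61, 54 or 48.

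**The case against.** The best defence concerns the clinical outcomes, and much of it stands.

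- **Month 48.** A reader might infer that 48-month outcomes cannot be obtained at all. The documents do not support that. The 15-, 30- and 45-month analyses are described as feedback to the programme team, while record retrieval and four cycles continue to Oct 2014 with a final report afterwards. Early enrollees can supply 48-month HbA1c and blood pressure. What remains is that the three listed full analyses stop short of month 48 and do not match the four cycles.
- **Untested time points.** A reader might infer that hypotheses 2 and 3 go untested at 24 and 48 months. They concern proportions at target, for which a paired t-test is not the natural method. Item 1 reports percentages achieving the outcome criterion, item 3 compares participants with controls, and item 4 compares cycles; none is restricted to 12 and 36 months. The annual repetition over five years points the same way. The accurate statement is that no paired test is assigned there.
- **Power.** Losing month 60 does not weaken the survey at its earlier visits; at 36 months power would be about 90%.
- **Importance.** The 60-month PRO are secondary, no hypothesis names month 60, and the primary outcomes do not depend on it.

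None of this answers the 60-month survey conflict or the mismatch between item 2 and Appendix C.

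**Conclusion.** The point holds for month 60. On the protocol's own dates, no survey patient reaches the 60-month interview before the calendar closes; the first intake misses it by about 6 to 9 months and later intakes by more. Appendix C's shorter PRO schedule and the absence of PRO collection after Jun 2011 compound the conflict. The cohort's Sept 2015 end likewise falls after the report. The consequence for size is a recruitment target of 550 per group justified by a visit that cannot be reported, against 415 if the last follow-up is at 36 months.

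It also holds that item 2 and Appendix C agree on clinical and service outcomes only at 12 and 36 months. For month 48 the conclusion is limited: no full analysis is listed at or after it, and data by Oct 2014 are confined to patients enrolled by about Oct 2010.

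This rests on the timeline dates as printed, two-sided alpha of 0.05, and the plan's 25% loss per follow-up. The calendar conflict depends on neither of the last two.

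**What to change.** 1. Split item 2: clinical and service outcomes at 12, 24, 36 and 48 months, matching hypotheses 2 and 3 and Appendix C; PRO at the survey visits.
2. Align Appendix C's PRO row with those survey visits.
3. Choose one horizon for the survey. Either schedule the 12-, 36- and 60-month calls and move the last extraction, analysis and report past the last planned visit and the cohort's Sept 2015 end. Or drop month 60 throughout and restate sample size and power for the last follow-up kept. At 36 months that is 415 per group, or 550 with about 90% power.
4. Add a final full analysis at or after month 48 and reconcile the three listed analyses with the four cycles, or state that 48-month results cover early enrollees only.

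Items 1, 2 and 4 are mostly wording, apart from any added analysis. Item 3 costs either a later report with further interviewing, to at least Jan 2016 for the first intake, or a shorter claimed horizon.
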